## 11.0 Study Design

### 11.1 \* Study design (Help Text updated 9/13):

We are proposing an 18-month RCT that collects survey and non-invasive biological data from caregivers accompanying children who are visiting a pediatric urgent care center. Our previous, similar RCT study data collection ended on 8/31/15 as scheduled. Though the social needs-focused intervention is now a routine, standardized part of the pediatric primary care setting, we are proposing a new urgent care-focused randomized controlled trial where we will enroll eligible patients solely from urgent care. In one arm, we will offer the intervention; in the other, we will offer written information on available community resources, which is already above the standard of care. All patients in both arms will be followed over a six month period to capture information about changes in their social needs and health outcomes. Participants will be randomized into intervention or control arms of the study using a stratified randomization method in the computer-based program REDCap.

Activities: Following consent at time of enrollment, at both baseline and 6 mo follow up, we will administer a survey and collect hair, saliva and buccal mucosal cell swabs (from child and adult caregiver).

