#### 14.7 Exclusion criteria:

- Non-English or non-Spanish speaking parent or legal gaurdian
- Parent or legal guardian under age 18
- Parent or legal guardian accompanying patient is not familiar with the child's living situation
- Currently receiving services from the Health Advocate program or have received Health Advocate services in the past six months
- Non-San Francisco resident
- Foster child or child in clinic for a child protective clearance exam
- In clinic for exam related to child abuse
- Clinic staff

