## 16.0 Procedures

**16.1 \* Procedures/Methods (Help Text updated 9/13) For clinical research list all study procedures, test and treatments required for this study, including when and how often they will be performed. If there are no clinical procedures, describe the Methods:**

All patients in ZSFG Peds Urgent Care during study hours meeting inclusion criteria will be asked by a designated study research assistant accompanied by a study designated trained SFGH Health Advocate Research Assistant (HARA) if they are interested in the study. (See Introduction Script attached.) If there is time in the urgent care private patient room (where there are often long waiting periods for providers), the research assistant will review consents and HIPAA authorization forms with family. Otherwise, following the clinic visit, the study research assistant will escort interested patient families to the ZSFG Health Advocate office on ZSFG 6A (on the same floor and down the hall from the urgent care clinic) for eligibility review and consent process. The study research assistant will assign eligible participants a study ID#, which will be stored in a password protected REDCap file on the study's encrypted and password-protected laptop.

The Research Assistant will review consent with eligible caregivers and patients old enough to participate in consent process. Consent will include documenting study ID, completing caregiver name and contact information and child MR#. (NB: Any duplicate MRN will not be eligible for participation.) One consent form will be used for participants randomized into the intervention arm or the control arm of the study (See attached).

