Consenting caregivers will be given a copy of the study consent forms. They will also be asked to review and sign a HIPAA authorization form to enable access to separate ZSFG HA surveys/follow up and other health care records. In addition to caregiver consent, children 7 and older also will complete assent forms. (See attached study assent forms.) With caregiver permission, children will be offered entertainment activities including bubbles and age appropriate books, games, and videos. Before caregivers complete health surveys with the Research Assistant and HARA, children 2 yo and over and all caregivers will be given a cup of water and asked to swoosh mouths with water and then swallow water. This needs to be completed 20 minutes before saliva and buccal mucosal cell collection. Following water swoosh, all participating caregivers will complete a baseline survey conducted by Research Assistant and HARA on REDCap using a computer tablet. (See attached documents for baseline and follow up surveys.) There is one self-completion portion of the survey, which includes the Patient Health Questionnaire (PHQ-8) and measures for social support and stress, that participants can read and complete themselves or ask for assistance on. After completing the survey, all participating caregivers and children then will have hair cortisol and oral buccal mucosal cell and saliva samples collected. Participants will then be randomized into the intervention arm or the control arm of the study.

Randomization will occur at the participant level using a stratified randomization method in the computer-based program REDCap. This stratified method will be used to ensure a balance of Spanish speaking families and English speaking families within the groups. After completing the study survey and biomarkers collection, the Research Assistant will leave participant dyads with the HARA for randomization. The HARA will randomly assign participants to either the intervention or the control group. The Research Assistant will have no knowledge of or access to participants' group assignments.

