If a family is randomized into the intervention group, the HARA will have access to the social needs screening results obtained through the health survey. The HARA will proceed with the health advocacy intervention following the procedures of the SFGH Health Advocacy program and attempt to address unmet needs identified by the caregiver in the survey. This involves working directly with these participants to identify and address any social needs the family may have such as access to food, living conditions and financial security. This may also include providing referrals to outside agencies, referral to legal aid within the clinic, help with applications for social benefits, or other services (See attached HARA Initial Action Plan and FollowUp Survey). Participants in the intervention group who are also ZSFG Pediatric Primary Care patients will have receipt of any direct assistance provided by the HARA documented in their child's medical record indicating services provided. All members of the intervention group will receive a written handout containing information about community resources related to the social needs we ask about in the survey.

The HARA will follow-up with members of the intervention group for a maximum of 3 months by telephone to continue to assess progress towards addressing social needs and to provide further help as needed. When relevant, HARA will send blank program forms to families or other publicly available program information via email or U.S. post to members of the intervention group. If a patient does not respond to telephone follow-ups for over 1 month, HARA may also send secure email to initiate follow-up contact.

If participant dyads are randomized into the control group, the HARA will provide the family with a written handout containing information about community resources related to the social needs we ask about in the survey.

Complete scripts for the biomarker specimen collections are found in Appendices A and B. Following surveys, hair, saliva and buccal mucosal cells will be collected non-invasively. These measures will be obtained immediately after enrollment and at the six month follow up timepoint.

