## Appendix B

### **Saliva and Buccal Mucosal Cell Sample Collection Procedure:**

As with the hair sample collection, the research assistant will collect the mother's saliva and buccal cell sample while the child is with his/her caregiver. Then the research assistant will collect the child's sample. The steps involved in collected samples of saliva and buccal cells are as follows:

1. Make sure the child or adult has no food or gum in his/her mouth.
2. Put on non-latex gloves
3. Pull open the package from one end
4. Remove one of the swabs from the tube
5. Ask child or mother to open his/her mouth; use a tongue depressor if necessary.
6. Insert the swab into the mouth and rub firmly against the inside of the cheek and/or underneath lower and upper lips.
7. Continue rubbing in broad strokes for approximately 30 seconds to 1 minute. For maximum DNA collection, expand the sampling area to both sides of the mouth and use both sides of swab.
8. Remove the swab from the mouth, slide the plastic cap over the swab handle, with the flat side of the cap facing upwards and the swab facing downwards.
9. Insert the swab into the clear plastic tube and push the cap in place.
10. Hold the cap firmly on the tube while pulling the swab handle outwards to release the swab material into the tube.
11. Close the cap; the tube is now completely sealed.
12. Insert saliva swab into mouth until saturated.
13. Remove swab and insert into plastic tube; close cap; the tube is now completely sealed.

After collection of biomarker hair and saliva/buccal mucosal cell samples, family will receive the first \$50 gift card for participation. At five months post-enrollment, research assistant will contact family by phone or email to arrange 6 month follow up visit (may occur no earlier than 5 months and no later than 9 months post enrollment). Participants will be contacted up to 5 times by phone and/or email to arrange in-person follow-up for repeat survey and biomarker collection activities.

At the six month visit, child and caregivers will meet with the Research Assistant in the same private room on 6A, an interview room located in the Clinical Research Services (CRS) facilitates located at SFGH hospital one floor below pediatric urgent care in unit 5B, or in another community location that ensures participants' confidentiality where surveys will be conducted and non-invasive biomarker specimens collected from caregiver and child (repeat of collection procedures as above.)

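### The only bar to repeat enrolment is the child's record number, so a control caregiver can re-enter with a sibling and be assigned the family-level intervention during follow-up

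*Protocol*

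**What the plan says.** - **Repeat enrolment.** Section 16.1 has one rule: "NB: Any duplicate MRN will not be eligible for participation". The sentence before it shows whose number is meant: "Consent will include documenting study ID, completing caregiver name and contact information and child MR". Caregiver name and contact details are recorded, but no rule uses them to detect a repeat caregiver.
- **Eligibility.** Sections 14.6 and 14.7 do not mention a caregiver or household already in the trial. The nearest criterion is the exclusion "Currently receiving services from the Health Advocate program or have received Health Advocate services in the past six months".
- **Control arm.** Section 16.1: "If participant dyads are randomized into the control group, the HARA will provide the family with a written handout containing information about community resources". Health advocacy services are offered to control families only after the 6-month visit.
- **Unit of randomization.** "Randomization will occur at the participant level using a stratified randomization method in the computer-based program REDCap". Language is the only stratification factor described.
- **Level of the intervention.** Navigators work with participants to "identify and address any social needs the family may have such as access to food, living conditions and financial security", for at most three months.
- **Timing.** Section 11.1 describes an 18-month trial. Appendix B within 16.1 says the follow-up visit "may occur no earlier than 5 months and no later than 9 months post enrollment".
- **Signs of what was intended.** Section 14.4 equates 724 dyads with 724 caregivers and 724 children, and 14.1 gives 1448 subjects. Section 21.2 refers to an index child and dates the record review from household enrolment.

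**The concern.** A sibling has a different record number, so the stated check passes. Three consequences follow from the rules as written.

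1. **Contamination of a control household.** If the second dyad is assigned to the intervention before the first dyad's follow-up, navigation reaches the household whose needs are being measured as a control outcome. This pulls the comparison toward no effect.
2. **Carry-over from a former intervention household.** The service exclusion looks back only six months. Navigation lasts at most three months, so such a family can become eligible again and its second dyad can draw control.
3. **One caregiver counted twice.** The number of social needs, caregiver mental health and caregiver cortisol (12.1, 14.4) would be recorded twice for the same person, possibly in opposite arms. The t-test behind the sample size assumes independent caregivers.

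**Working it through.** **Step 1: does the text allow the route?**
- Child's record number: a sibling's is new, so the check passes.
- Sections 14.6 and 14.7: no caregiver or household limit, so the family passes.
- Prior-service exclusion: a control has had a handout and no navigation before the 6-month visit, so it is not triggered.
- Exposure window for the first control dyad: from enrolment to its follow-up visit, 5 to 9 months. Later re-enrolment no longer contaminates that dyad but still duplicates the caregiver.
- Reverse route: at most 3 months of navigation plus a 6-month look-back gives 9 months, which is less than the 18-month trial. An early intervention family can therefore re-enter.

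**Step 2: reproduce the plan's own figures (14.4).** Inputs: two-sided alpha 0.05, power 0.80, d = 0.25, 30% attrition.
- n per arm = 2(1.960 + 0.842)² / 0.25² ≈ 251.2, rounded up to 252. The t-test version gives 252.1, rounded up to 253. The plan uses 253.
- 253 / 0.70 = 361.4, rounded up to 362 per arm and 724 in total, as stated.
- Power at 253 per arm and d = 0.25 is 0.801 (t-test) or 0.803 (normal approximation).

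The stated sample size is correct and has almost no reserve at d = 0.25.

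**Step 3: dilution scenario.** Let s be the share of control caregivers who re-enrol with a sibling during follow-up. The protocol gives no such rate, so s is assumed, from 2% to 20%. Under 1:1 allocation s/2 of control dyads are contaminated. If these receive the whole effect, the contrast becomes d(1 − s/2).

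| s (assumed) | diluted d, from 0.25 | power, t-test | power, normal | n per arm for 0.80 (normal) |
|---|---|---|---|---|
| 0 | 0.2500 | 0.801 | 0.803 | 252 |
| 2% | 0.2475 | 0.793 | 0.795 | 257 |
| 5% | 0.2438 | 0.781 | 0.783 | 265 |
| 10% | 0.2375 | 0.760 | 0.762 | 279 |
| 20% | 0.2250 | 0.714 | 0.716 | 311 |

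**Step 4: the effects the plan expects.** Section 14.4 anticipates 0.26 to 0.43 SD for social needs and 0.38 to 0.46 SD for cortisol. T-test power at 253 per arm:

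| d | s = 0 | s = 10% | s = 20% |
|---|---|---|---|
| 0.26 | 0.831 | 0.792 | 0.748 |
| 0.38 | 0.989 | 0.982 | 0.970 |
| 0.43 | 0.998 | 0.996 | 0.991 |

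Of these, only the value at the bottom of the social-needs range falls below 0.80.

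**Step 5: distinct caregivers.** If both records of each re-enrolled control caregiver are among the 506 analysed, distinct caregivers number 506 − 253s. That is about 501 (s = 2%), 481 (10%) or 455 (20%). The power figures above do not include this loss of independence.

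**The case against.** The best defence is that one dyad per family was clearly intended. The counts in 14.1 and 14.4 and the household wording in 21.2 make sense only on that reading. The screening script, surveys and consent forms are attachments not shown, and staff may well recognise returning families. This is fair. It means the document does not support the inference that the trial was designed to admit families twice, or that contamination has occurred. It does not close the gap, because an intention that appears only in a head count does not operate as an eligibility check.

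Four further inferences are tempting and go too far:

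- **That the trial is underpowered.** The sample size reproduces. The losses rest on an assumed s and on full transfer of the effect. Navigation lasts up to three months, so a sibling enrolled shortly before the first dyad's visit could hardly pass on the whole effect. For each s, the dilution figure is an upper bound.
- **That all outcomes suffer.** At the effects expected for cortisol the loss is negligible.
- **That contamination runs only into control households.** The six-month exclusion blocks intervention families only for a time, so carry-over in the other direction is also possible.
- **That repeat caregivers will be analysed as independent.** Section 12.3 plans mixed models and GEE, which can take a household cluster, and the clustering level may properly be left to an SAP. The protocol does not say that independence will be assumed.

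**Conclusion.** The point holds as a gap in the eligibility rules. As written, they let a control caregiver re-enrol with a sibling and receive family-level navigation before the first dyad is assessed, and they do not guarantee the 724 distinct caregivers that 14.4 counts. Contamination of a control dyad biases toward no effect.

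The gap is certain from the text, but its frequency is not known. At the minimum detectable d = 0.25 the upper-bound loss runs from under one percentage point of power (s = 2%) to about nine (s = 20%). At d = 0.38 or more, power stays at about 0.97 or higher throughout. These figures assume equal allocation of the second dyads, full effect transfer and re-enrolment before the first follow-up. They leave out the correlation between two records of one caregiver. The correction is worth making because it costs almost nothing and belongs in the protocol's own criteria.

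**What to change.** Add to 14.7, and in place of the record-number note in 16.1: *One dyad per household; a caregiver or child from a household already enrolled is ineligible.* Check this before randomization against the caregiver name and contact details already recorded at consent. The look-up should return only whether the household is enrolled, not its arm, so that the Research Assistant stays unaware of assignments.

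The cost is one criterion and one look-up in data already held. A few repeat families become ineligible, against 3000 people expected to be consented and screened (14.3). No stated sample size changes.

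If any household has already enrolled twice, keep all dyads as randomized and use household-clustered standard errors for the non-independence. Add a sensitivity analysis that excludes households with dyads in both arms. Neither step undoes contamination that has already happened, and keeping only the first dyad would retain exactly the control dyad that was exposed. The added criterion is the only part that prevents the problem.

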## **16.2 Interviews, questionnaires, and/or surveys will be administered or focus groups will be conducted:**

☒ Yes ☐ No

List any standard instruments used for this study:

Patients eligible for enrollment, who consent to be in the study, will be subject to:

a. Social, physical and mental health status and health care utilization survey conducted via laptop using REDCap. (See attached baseline and follow up surveys.) Survey is administered in person by fully

bilingual English/Spanish research assistants. There is a short section with depression, social support and stress measures typically collected by self-report at the end of both baseline and follow up survey where patients can self-complete while research assistant is available for assistance.

b. Follow-up surveys will be conducted at 6 months post study enrollment, again by bilingual English /Spanish research assistants. (See attached follow up survey.) Research Assistant will call or email a maximum of 3 times each to arrange or conduct phone follow-up. If there is no response to the phone calls and email, patients will receive a letter addressed to the address of record asking them to phone the research line if they are willing to complete the study survey. Each survey is anticipated to last a maximum of 20 minutes. After each survey administration and biomarker collection, participating families will receive \$50 VISA gift card.

For patients who are unable to attend a follow-up visit in-person, but are still willing to participate in the study, the Research Assistant will offer to complete the survey by phone or provide patients with an online link to the survey. Patients who complete only the survey and do not come in for biomarker collection will receive a \$25 VISA gift card.

Caregivers who consent to participate in the follow-up key informant interview will complete a 60-minute in-person qualitative interview with a Research Assistant about their experiences working with the health advocate patient navigator and accessing services. Participants who complete the key informant interview will receive a \$25.00 VISA gift card.

All Research Assistants will complete CITI and HIPAA training in addition to receiving training in research /consent rules and regulations, cultural sensitivity, legal and social needs screening and intervention, as well as survey administration techniques.

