**24.3 \* How, when, where and by whom potential subjects will be approached:**

Caregivers will be approached in the urgent care patient clinic room or waiting room by the study research assistant and a study designated trained ZSFG Health Advocate research assistant and asked whether they are interested in talking about participating in a study on the effectiveness of the ZSFG hospital Health Advocate program. If so, patients will be screened for eligibility. In clinic rooms, while waiting for the provider, the research assistant will consent eligible families and complete study activities with the assistance of the study designated ZSFG Health Advocate research assistant. If the clinic visit ends before study activities are completed, the research assistant and the designated ZSFG Health Advocate research assistant will walk the family down the hall to the research office where the remaining study activities will occur. All study activities will be deferred for provider-patient interactions. This is how we ran our initial study in the Peds Primary and Urgent Care Clinics and this was well-received by clinic staff.

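### The navigator (HARA) helps conduct the baseline needs survey for every family, so control families' needs are known to the person who then hands them the generic handout

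*Protocol*

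**What the plan says.** Section 16.1 of the Protocol sets out the enrollment visit in order.

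- **Survey.** The HARA (Health Advocate Research Assistant) takes part for every family: "all participating caregivers will complete a baseline survey conducted by Research Assistant and HARA on REDCap using a computer tablet". The section says so a second time when it schedules the water rinse: "Before caregivers complete health surveys with the Research Assistant and HARA". Section 24.3 agrees that families "complete study activities with the assistance of the study designated ZSFG Health Advocate research assistant".
- **Self-completed part.** One portion can be filled in by the caregiver. It is described as covering the PHQ-8, social support and stress. Social needs are not listed in it.
- **Randomization.** After survey and specimens, "the Research Assistant will leave participant dyads with the HARA for randomization". Then "The HARA will randomly assign participants to either the intervention or the control group", using REDCap. The Research Assistant is kept unaware of the assignment.
- **Intervention arm.** "If a family is randomized into the intervention group, the HARA will have access to the social needs screening results obtained through the health survey". Work with the family on those needs follows, with telephone follow-up by the HARA for up to 3 months.
- **Control arm.** "If participant dyads are randomized into the control group, the HARA will provide the family with a written handout" on community resources. Intervention families receive a handout too. Control families are offered advocacy services only after the 6-month visit.

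Section 14.4 names number of social needs as the primary parent-reported outcome.

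**The concern.** The trial compares personal navigation plus a handout with a handout alone. The comparison depends on control families receiving no navigation before the 6-month visit. The protocol takes care on one side of this, since the Research Assistant never learns the assignment. On the navigator's side, the only related wording is the sentence that links HARA access to the screening results with an intervention assignment. If the HARA has already sat through the needs questions with every family, that link has no practical effect for control families.

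A trained navigator who has just heard that a family is short of food or facing a housing problem, and who is then with that family without the Research Assistant, can easily point to the right line of the handout or offer advice. Any such help would lower the number of social needs in the control arm and shrink the between-arm difference on the outcome the HARA is there to change. Analysis cannot reliably undo this afterwards, so it is best dealt with in the enrollment procedure.

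**Working it through.** **Step 1: set the sections side by side.**

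| Question | What the Protocol says | Where |
|---|---|---|
| Who conducts the baseline survey? | Research Assistant and HARA, for all caregivers, before randomization | 16.1 (twice); 24.3 consistent |
| Are the needs items self-completed? | Not listed in the self-completed part | 16.1 |
| When does the HARA get the needs results? | Stated only for families assigned to intervention | 16.1 |
| Who is with the dyad at and after assignment? | The HARA, the Research Assistant having left | 16.1 |
| Who gives control families the handout? | The HARA | 16.1 |

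The first two rows mean that, as far as the text shows, the HARA is party to the needs interview for control families. The third row then cannot work as a restriction. Nothing in the document takes the HARA out of the needs section for any family, and nothing limits what the HARA may say when giving the handout.

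**Step 2: reproduce the plan's power figure.** Inputs from section 14.4: 724 dyads, 30% attrition, two-sided alpha 0.05, d = 0.25.

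- Retained: 724 × 0.70 = 506.8, stated as 506, which is 253 per arm.
- Power = Φ(d × √(n/2) − 1.96) = Φ(0.25 × √126.5 − 1.96) = Φ(2.812 − 1.960) = 0.803.
- Required per arm for 80%: 2 × (1.960 + 0.842)² / 0.25² = 251.2, so 252.

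The stated figure of at least 80% holds, with almost no margin at d = 0.25.

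**Step 3: sensitivity to dilution.** The Protocol gives no contamination rate, so the inputs here are assumptions. If a share f of control families receives help worth a fraction c of the full effect, the observed difference becomes d × (1 − f × c). With f from 0.10 to 0.30 and c = 0.5, the shrinkage is 0.10 × 0.5 = 5% to 0.30 × 0.5 = 15%. Power with 253 per arm:

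| True d | No shrinkage | 5% | 10% | 15% |
|---|---|---|---|---|
| 0.25 (minimum in 14.4) | 0.80 | 0.76 | 0.72 | 0.67 |
| 0.26 (low end expected for social needs) | 0.83 | 0.79 | 0.75 | 0.70 |
| 0.345 (midpoint of 0.26 and 0.43) | 0.97 | 0.96 | 0.94 | 0.91 |
| 0.43 (high end expected) | 1.00 | 1.00 | 0.99 | 0.98 |

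For example, 0.25 × 0.85 = 0.2125, and Φ(0.2125 × √126.5 − 1.96) = Φ(0.430) = 0.67. The table shows how sensitive the design is. It is not evidence that contamination occurs.

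**The case against.** The strongest reply is that the access sentence describes the intervention workflow and not a barrier. It never says that the HARA is denied control families' results, and it is not presented as protection against contamination. What limits control contact is the direct instruction that control families receive a written handout. This is fair as far as it goes. The restriction is the natural reading of a conditional sentence, not an explicit prohibition. But without it the Protocol has no stated limit on the navigator's knowledge, and the handout instruction does not say that advice is to be withheld.

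A second reply is that the mechanism is weak. Navigation means referrals, help with applications and up to 3 months of calls, while the handout already covers the surveyed needs and caregivers know their own situation. A passing remark may be worth far less than half the effect. This stands, and it is why the size is given only as a sensitivity.

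Third, changing who runs the survey leaves the HARA with control dyads at assignment, where needs can still come up. That is correct, so the fix reduces the opportunity and does not close it.

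Four stronger readings are tempting but not supported:

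- **A contradiction with section 16.2.** That section says "Survey is administered in person by fully" bilingual research assistants. A HARA is by title a research assistant, so this leaves the HARA's share of the interview unclear but does not conflict with 16.1.
- **Help to controls could never be detected.** Section 16.1 requires charting only for intervention families who are also primary care patients. But section 13.1 describes a client management database for the advocacy program, 16.1 provides for access to its surveys, and the follow-up survey is attached but not shown. Whether these would capture help to control families cannot be judged. No section of the document expressly provides for recording it.
- **Bias in every outcome.** Dilution would affect only outcomes that the intervention changes. Number of social needs is the most direct.
- **Predictable allocation.** The assignment comes from REDCap. Knowing a family's needs does not by itself let the HARA foresee it.

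**Conclusion.** The point holds as an avoidable weakness in the enrollment procedure. Sections 16.1 and 24.3 have the person who delivers the intervention help conduct the needs survey for every family before assignment. That same person then randomizes control families and gives them the handout without the Research Assistant. The wording that ties the screening results to an intervention assignment cannot, on its natural reading, keep control families' needs from the HARA.

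The size is unknown. Under the assumed 5% to 15% shrinkage, power at d = 0.25 falls from 0.80 to between 0.76 and 0.67. At the midpoint of the expected range it stays above 0.90. The conclusion rests on two readings of the text: that the needs items fall in the interviewed part of the survey, and that the access sentence is meant as a condition.

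**What to change.** Make three changes to the Protocol:

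1. Amend sections 16.1 and 24.3 so that the Research Assistant alone administers the social needs items, with the HARA joining for the randomization step.
2. Set REDCap user rights so that the needs items open to the HARA only after an intervention assignment has been returned, and say so in 16.1.
3. State in 16.1 that control families receive the handout without tailored advice, and that any help given to a control family before the 6-month visit is recorded.

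The cost is a few sentences and a permission setting, with no added staff. The Research Assistant's blinding is unaffected. The downsides are that one person runs the 15 to 20 minute survey, in a visit that may be interrupted by clinical care, and that the HARA reads intervention families' needs instead of hearing them. Because the HARA still meets control families, some risk remains. The recording requirement would let the trial team see how large it is.
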